Art plays a significant role in health promotion, and it is a method of healing. The arts are an essential part of health and nursing care because they are beneficial in disease prevention, cure, rehabilitation and care [13]. Expressive art therapy (EAT) has been incorporated into various programs as an element of both foundational and supportive treatment. EAT combines physical and psychological nonmainstream methods, including dance/movement, drawing, painting, sculpting, music, writing, sound, and improvisation [13]. EAT provides participants of all ages with a platform to release feelings, increase self-awareness, and explore hidden feelings in a supportive setting [14]. The participants do not need any experience or skills in art making, but the expressive art therapists need them. Considering cultural differences, expressive arts therapists should be culturally competent [15]. EAT has been applied in cancer patients, psychiatric patients, neurosurgical patients, pediatric patients, and domestic violence survivors [15, 16], but very few studies have explored the effectiveness of EAT in infertile women. As reported, releasing infertility-related stress is a way to promote the mental health of infertile women, which is essential to improve the outcomes of infertility treatments. Therefore, we designed a randomized controlled trial to verify the effectiveness of EAT in infertile women. We hypothesize that EAT will decrease the levels of infertility-related stress, depression and anxiety in infertile women.

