### Primary and secondary outcomes

The primary outcome is the level of infertility-related stress measured by the Fertility Problem Inventory (FPI), before participants are discharged from the hospital. The secondary outcomes are the levels of anxiety and depression measured by the Hospital Anxiety and Depression Scale (HADS) before participants are discharged from the hospital.

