### Sample size

According to the pilot study, the standard deviations of FPI in the intervention group and control group were 22.91 and 29.01, respectively, and the means of FPI in the intervention group and control group were 144.29 and 159.31, respectively. We assumed that the number of patients in the intervention group was the same as that in the control group. The calculated sample size of 52 participants per group would provide 80% power with a two-tailed alpha error of 0.05. Estimating a dropout rate of approximately 5%, we will recruit at least 55 participants in each group.

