### Statistical methods

The qualitative data (demographic characteristics) will be statistically described by number (*n*) and percentage (%) and statistically be inferred by chi-square test. The Shapiro–Wilk test will be used to assess the normality of our data. This test is suitable for small to medium-sized samples and will help us determine whether the data follows a normal distribution. The quantitative data (scores of HADS and FPI) will be described by mean/median and standard deviation (SD)/interquartile range (IQR) and be inferred by *t* test/rank sum test. In all analyses, a *P* value of < 0.05 indicates statistical significance. To handle protocol non-adherence in our randomized controlled trial, we will use an intention-to-treat (ITT) analysis. Additionally, we will conduct a per-protocol (PP) analysis to include only those participants who fully adhered to the study protocol. By comparing ITT and PP results, we aim to understand the impact of adherence on study outcomes. All instances of non-adherence will be documented and considered during data analysis and interpretation. SPSS 21.0 (SPSS Inc., Chicago, IL) will be used for statistical analysis.

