## Discussion

Infertility has several health and social consequences, including poor physical and mental well-being, disease stigma, violence from family, marriage breakdown, and economic pressure [22]. Infertility affects the mental well-being of more women than men. Infertile women had higher levels of infertility-related stress, anxiety, and depression than infertile men [5, 8]. Infertile women coping with stress might benefit by disclosing their experience of infertility, so mental care needs to encourage the expression and sharing of emotions during treatment [11, 12]. Expressive art therapy (EAT) has been incorporated into various programs as an element of both foundational and supportive treatment. EAT combines physical and psychological nonmainstream methods, including dance/movement, drawing, painting, sculpting, music, writing, sound, and improvisation [13]. This diversity of intervention methods caters to the varied needs of patients, providing a more comprehensive and adaptable treatment framework. Moreover, this study underscores the significance of cultural sensitivity among expressive art therapists, which is instrumental in effectively engaging patients from Chinese cultural backgrounds, thus enhancing the efficacy of interventions.

This study will employ a randomized controlled trial design, bolstering internal validity. Randomly assigning participants to either the intervention or control groups serves to mitigate the impact of selection bias, heightening the reliability of our results [23]. Additionally, the study will use robust measurement tools such as the Hospital Anxiety and Depression Scale (HADS) and the Fertility Problem Inventory (FPI) for assessing anxiety, depression, and infertility-related stress. These instruments have demonstrated validity and reliability in prior research, ensuring the robustness and comparability of our findings [18, 19, 21].

Thus, our study will verify the effectiveness of EAT for anxiety, depression, and infertility-related stress in infertile women. If our hypothesis is supported, this study will provide valuable information on mental health care strategies for infertile women and inform the design of future research and programs focused on infertility-related stress interventions.

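### The blanket P < 0.05 rule and the promise to verify effects on all three scores leave the secondary anxiety and depression claims without error control; the primary FPI test is unaffected

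*Protocol article*

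**What the plan says.** The Primary and secondary outcomes section sets a clear ranking. On the FPI: "The primary outcome is the level of infertility-related stress measured by the Fertility Problem Inventory (FPI), before participants are discharged from the hospital". On the HADS: "The secondary outcomes are the levels of anxiety and depression measured by the Hospital Anxiety and Depression Scale (HADS) before participants are discharged". The Sample size section attaches its error rate to the FPI, because the calculation uses FPI means and standard deviations only: "The calculated sample size of 52 participants per group would provide 80% power with a two-tailed alpha error of 0.05".

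The Statistical methods section does not carry the ranking into the decision rule. HADS and FPI scores are treated together and will "be inferred by *t* test/rank sum test", and the threshold is general: "In all analyses, a *P* value of < 0.05 indicates statistical significance".

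Two other places put the three scores on an equal footing. The Background states: "We hypothesize that EAT will decrease the levels of infertility-related stress, depression and anxiety in infertile women". The Discussion concludes: "our study will verify the effectiveness of EAT for anxiety, depression, and infertility-related stress in infertile women".

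**The concern.** Taken together, these statements mean that the primary/secondary ranking has no stated consequence for what may be concluded. Suppose the FPI comparison is null and HADS anxiety gives P = 0.03. Under the stated threshold that result is significant, and under the Discussion's wording it could be reported as verified effectiveness for anxiety. A plan that treated the HADS scores as supportive, or tested them only after the FPI, would not allow this.

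At stake is the error rate behind two of the three promised claims, not the validity of the primary test. The article also plans an interim analysis at about half of completion. That is a separate source of multiplicity and is not counted here.

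**Working it through.** **The plan's own figure.** The article states no family-wise error rate, so there is none to reproduce. Its only figure tied to alpha is the sample size.
- Difference: 159.31 − 144.29 = 15.02.
- Pooled SD: √((22.91² + 29.01²)/2) = 26.14.
- n per group = 2 × (26.14 × (1.960 + 0.842)/15.02)² = 47.5, so 48 by normal approximation and 49 by t test.
- The stated 52 is not reproduced by these. It is on the safe side: power at 52 is 82.7% by t test. Inflating 49 for a rank sum test (× π/3) gives 51.3, so 52, but the article does not say this was done.
- Dropout: 52/0.95 = 54.7, so 55, as stated.

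None of this bears on the point. It confirms only that the 0.05 in the Sample size section belongs to the FPI.

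**Inputs for the error rate.** Three scores (FPI, HADS anxiety, HADS depression), each tested two-sided at 0.05, so c = 1.96. The correlation ρ between the test statistics is not given. I assume one common value and show a range from 0 upwards.

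**Formulas, with no true effect on any score** (φ and Φ are the standard normal density and distribution function):
- Independent tests, benefit only: 1 − 0.975³ = 7.3%.
- Independent tests, either direction: 1 − 0.95³ = 14.3%.
- Correlated tests, benefit only: 1 − ∫ φ(u) [Φ((c − √ρ·u)/√(1−ρ))]³ du.
- Correlated tests, either direction: the same, with the bracket replaced by Φ((c − √ρ·u)/√(1−ρ)) − Φ((−c − √ρ·u)/√(1−ρ)).

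| Assumed ρ | At least one false benefit, 3 tests | At least one false positive, either direction, 3 tests | Either direction, 2 HADS tests only |
|---|---|---|---|
| 0 | 7.3% | 14.3% | 9.8% |
| 0.3 | 6.8% | 13.6% | 9.5% |
| 0.5 | 6.3% | 12.5% | 9.1% |
| 0.7 | 5.5% | 10.9% | 8.3% |
| 0.9 | 4.2% | 8.4% | 7.0% |
| One test alone | 2.5% | 5.0% | – |

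The benefit-only column is the relevant one, because the promise is to verify effectiveness.

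**The part due to the HADS scores.** Subtracting the FPI's own 2.5% gives the chance that a HADS score shows a false benefit while the FPI shows none: 7.3 − 2.5 = 4.8% at ρ = 0, 6.3 − 2.5 = 3.8% at 0.5, and 4.2 − 2.5 = 1.7% at 0.9.

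**With the FPI tested first.** If no HADS claim can be made unless the FPI test is significant at two-sided 0.05, then with no true effect the chance of any confirmatory false positive equals that of the FPI test, 5% in both directions together. If the FPI effect is real, Holm holds the two HADS tests to 5% between them.

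**The case against.** Four arguments stand against the point.

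- **A full protocol or analysis plan may set the order of testing.** This is right as far as a missing hierarchy goes: a journal article commonly leaves that to the fuller document, and its absence is no fault. What remains is what the article does state. It fixes 0.05 for every analysis, so a plan that tested the HADS scores conditionally or at a stricter level would contradict it, and the Discussion's claim is the article's own wording.
- **There is one primary outcome, and secondary outcomes are often reported at nominal 0.05.** Also right, and it limits the point. The FPI test keeps its own 5% across outcomes. Nominal reporting is acceptable when secondary results are supportive, but the Background and Discussion do not describe them so.
- **The three scores are joined by *and*, and the Discussion goes on to speak of a single hypothesis.** If all three had to be significant, the error would be at most 5% and there would be no inflation. No section states that requirement, and significance is declared test by test. The any-of-three reading is therefore open but not established. The threshold sentence itself does not say that a lone HADS result proves effectiveness; that follows only when it is joined to the Discussion.
- **The larger figure is easy to overstate.** A reader might infer that the trial's false-positive rate is 12.5% instead of 5%. The documents do not support that. The 12.5% needs an assumed correlation of 0.5, counts false harms as well as false benefits, and is set against a 5% family-wise guarantee that the article never gives.

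**Conclusion.** The defect is a stated rule that disregards the article's own ranking of outcomes, combined with confirmatory wording for all three scores. As written, an isolated HADS result could be presented as verified effectiveness.

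On the any-of-three reading, with no true effect and non-negative correlations, the chance of at least one falsely verified benefit is at most 7.3%, or about 2.9 times the 2.5% for one test (7.3/2.5). It falls as the scores correlate more closely. Counting both directions, the ceiling is 14.3%. Neither figure is a property of the primary analysis, and neither applies if all three scores must be significant.

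Severity is minor to moderate: the FPI conclusion stands, while the claims for anxiety and depression need either error control or more modest wording.

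**What to change.** In the Statistical methods section, replace the general threshold with a rule that rests the confirmatory claim on one analysis: the intention-to-treat comparison of FPI at discharge, two-sided 0.05. It must be a single named comparison, because the section plans both intention-to-treat and per-protocol analyses and allows either of two tests. Only one FPI P value should decide.

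For HADS anxiety and HADS depression, choose one of two equally acceptable routes:

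1. Report them as supportive estimates with 95% confidence intervals and make no confirmatory claim.
2. Test them for confirmatory purposes only if that FPI test is significant, using Holm (smaller P against 0.025; if that passes, larger P against 0.05). Otherwise report them as in route 1.

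In the Discussion, limit the promise of verification to infertility-related stress, and extend it to anxiety or depression only if they pass this sequence. Date the change before any comparative results are seen.

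The cost is a few sentences. No extra participants or data are needed, and the FPI keeps its full 0.05 and its power. The small downside is that a HADS result alone can no longer be called confirmatory and, under route 2, the first HADS test faces 0.025 instead of 0.05.

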**Methods:**

This study is a randomized controlled trial. Participants in the intervention group will receive expressive art therapies after the baseline investigation. Expressive art therapies will be led by the certified international expressive art therapist. The interventions include progressive muscle relaxation training, music meditation and drawing therapy. Participants in the control group will receive routine care. The Hospital Anxiety and Depression Scale (HADS) and Fertility Problem Inventory (FPI) will be used to investigate the anxiety, depression, and infertility-related stress of all participants at admission and at discharge.

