### Intervention

Expressive art therapies will be led by the certified international expressive art therapist. The interventions include progressive muscle relaxation training, music meditation, and drawing therapy. The intervention time points include the first 24 h of admission (t_1_) and the first 24 h after surgery (t_2_). After baseline investigation (t_0_), participants in the intervention group will receive progressive muscle relaxation training (10 min), music meditation (10 min), and drawing therapy (40 min). The total duration of intervention is approximately 1 h. Participants in the intervention group and control group will receive general health education and routine nursing care. General health education and routine nursing care are standard practices in our hospital. By using them as the control group, we can establish a baseline for comparison, which makes it easier to evaluate the effectiveness of our intervention. Within the first 24 h after surgery, participants in the intervention group will perform progressive muscle relaxation and music meditation under guidance. At discharge (t_3_), participants in the two groups will complete the questionnaires. Participants are free to leave the study at any time for any reason without consequences. To improve adherence, all participants will be provided with guidance when they sign the informed consent form and commit to attending on the scheduled intervention time points.

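### The gap between ITT and per-protocol results cannot be read as the impact of adherence, because attendable sessions exist only in the intervention arm

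*Protocol article*

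**What the plan says.** The Statistical methods section gives ITT the main role: "To handle protocol non-adherence in our randomized controlled trial, we will use an intention-to-treat (ITT) analysis". It then adds "a per-protocol (PP) analysis to include only those participants who fully adhered to the study protocol" and gives the purpose of having both: "By comparing ITT and PP results, we aim to understand the impact of adherence on study outcomes". It goes on to say that non-adherence will be recorded and taken into account in analysis and interpretation. No criteria for full adherence are given by arm, and the only inference named for FPI and HADS scores is a t test or rank sum test.

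The Intervention section describes what each arm has to do. After baseline, the intervention arm has about one hour of relaxation training, music meditation and drawing. A second session follows: "Within the first 24 h after surgery, participants in the intervention group will perform progressive muscle relaxation and music meditation under guidance". For the other arm, the abstract says "Participants in the control group will receive routine care", and the Intervention section makes that care common to both: "Participants in the intervention group and control group will receive general health education and routine nursing care". Both arms complete the discharge questionnaires.

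**The concern.** An ITT-PP contrast isolates adherence only if those who adhere and those who do not would have had the same outcome anyway. Nothing in this design makes that likely. One of the two sessions falls in the first day after surgery, when pain, recovery or distress could influence both whether a woman takes part and what she scores on the FPI at discharge. A control has no session to miss. Removing non-adherers therefore changes the make-up of one arm and leaves the other almost whole, so randomisation no longer protects the comparison.

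At stake is a secondary conclusion. A PP difference larger than the ITT difference could be taken to show that fuller participation helps, and a smaller one that it does not. Either pattern can arise from who drops out of the PP set.

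**Working it through.** **The plan's own figure.** The Sample size section gives FPI means of 144.29 and 159.31 (difference 15.02), SDs of 22.91 and 29.01, 80% power, two-sided alpha 0.05, and 52 per group. The pooled SD is √((22.91² + 29.01²)/2) = 26.14.
- Normal formula: 2 × (26.14 × (1.960 + 0.842)/15.02)² = 47.5, so 48 per group. The exact t-test calculation gives 49.
- Dividing the t-test figure by the rank-sum efficiency 3/π gives 51, close to the stated 52.
- Dropout: 52/0.95 = 54.7, so 55, as stated.

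The point below does not depend on which of these was used. The figures serve only to set the scale.

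**Which arm the filter acts on.**
- Intervention arm: a woman can miss either session, or leave, or not answer the discharge questionnaire.
- Control arm: a woman can leave or not answer the questionnaire. She then has no discharge FPI for the ITT comparison either, so unless her outcome is imputed she adds little to the ITT-PP gap.
- Room sharing across arms (Participants section) removes both women from the study, one from each arm. It is not an adherence filter.

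**Bias when the treatment does nothing.** Let *a* be the proportion of the intervention arm kept in the PP set, and *g* the number of FPI points by which non-adherers would exceed adherers regardless of treatment. Both are assumptions. The mean of the whole arm is *a* × m + (1 − *a*) × (m + *g*), where m is the mean in adherers. So m lies (1 − *a*) × *g* below the mean of the whole arm, which under no effect equals the control mean. Hence:
- bias = (1 − *a*) × *g*
- SE = √(22.91²/(52*a*) + 29.01²/52)
- type I error of the PP test = Φ(−1.96 + bias/SE) + Φ(−1.96 − bias/SE)

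| *a* | *g* | Bias (FPI points) | SE | Type I error |
|---|---|---|---|---|
| 95% | 10 | 0.5 | 5.18 | 5.1% |
| 95% | 15 | 0.75 | 5.18 | 5.2% |
| 90% | 10 | 1.0 | 5.23 | 5.4% |
| 90% | 15 | 1.5 | 5.23 | 6.0% |
| 80% | 10 | 2.0 | 5.37 | 6.6% |
| 80% | 15 | 3.0 | 5.37 | 8.6% |
| 70% | 15 | 4.5 | 5.53 | 12.9% |

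A smaller gap matters less: at 80% with *g* = 5 the bias is 1.0 point and the type I error 5.4%. If non-adherers would score lower instead, the sign of the bias reverses and its size stays the same.

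**Check with a different selection model.** Let non-adherence have correlation ρ with the FPI score a woman would have had anyway, with SD 26.14 and normal selection. Under no effect, for ρ from 0.1 to 0.5, the expected PP difference is 0.3 to 1.4 points at 95% adherence, 0.5 to 2.6 at 90%, 0.9 to 4.6 at 80% and 1.3 to 6.5 at 70%.

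**Can the contrast tell the two apart?** Suppose instead that there is no selection, that adherers gain the full 15.02 points and that non-adherers gain nothing. The ITT-PP gap is then (1 − *a*) × 15.02, which is 0.75, 1.5, 3.0 and 4.5 points at 95, 90, 80 and 70%. At every adherence rate this lies inside the range that selection alone can produce. An observed gap of a given size fits either account.

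**The case against.** The strongest reply is that little hangs on this analysis. ITT is the stated way of handling non-adherence, PP is additional, and neither the primary outcome nor the sample size depends on it. That stands. A reader might infer that the trial's main result is biased, or that its false-positive rate is raised. The article does not support that: the type I errors above belong to the PP test alone.

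Four further limits also stand.

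- **How far the text commits.** A reader might infer that a larger PP effect will be reported as proof that adherence works. The article states an aim to understand the impact of adherence and says that non-adherence will be considered in interpretation. It does not announce that conclusion. It also names no method that would separate adherence from selection, so the stated aim remains out of reach.
- **Filtering of one arm only.** This is inferred from the sessions, not stated. Full adherence to the protocol could also cover eligibility violations or undetected contamination, which can occur in controls. The detailed PP definition may stand in a document not shown. But a definition would not make the contrast an estimate of the effect of adherence.
- **Direction.** A reader might infer that the bias favours the therapy. Nothing in the article shows whether more or less distressed women would miss sessions.
- **Size.** The article gives no adherence rate. The programme is short and delivered to inpatients, so adherence of 90 to 95% is quite possible, and the bias is then 0.5 to 1.5 points. A 15-point gap is itself as large as the planned effect.

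**Conclusion.** The point holds as a fault in the stated interpretation of a supplementary analysis. Following the plan as written, the ITT-PP gap would mix any effect of adherence with selection of uncertain direction. This conclusion needs only that missed sessions fall mainly in one arm and may be related to outcome. The size is conditional on assumed inputs: negligible to small at 90 to 95% adherence, and 2 to 4.5 FPI points (13 to 30% of the planned 15.02) in the 70 to 80% rows tabulated for 10 to 15 point gaps. The ITT comparison stands as planned. Because the correction costs almost nothing and changes what the trial may claim about adherence, it should be made.

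**What to change.** Present the PP result as a descriptive sensitivity analysis, and delete the sentence that infers the impact of adherence from ITT against PP. This is a change of wording only.

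Optionally, if an effect in adherers is wanted, estimate a complier average causal effect with randomised group as instrument for attendance. If no control takes part in the therapy, the version without covariates is the ITT difference divided by the proportion attending. For example, an ITT difference of 12.02 with 80% attending gives 12.02/0.80 = 15.02. Non-adherence is already to be documented, so this needs one extra model and no new data collection. What counts as attending must be fixed in advance, because there are two sessions with different content.

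Its downsides should be stated with it. The confidence interval is wider. The exclusion restriction is strained in two ways: a woman coded as non-attending may have benefited from one session, and participants know their allocation (Blinding section) and report the outcome themselves (Measurement section), so allocation alone could shift scores. For these reasons it is an option, not a requirement.
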